#### Methods for additional analyses (e.g., subgroup analyses) {20b}

Subgroup analyses will be conducted according to surgical access (open vs. minimally-invasive), kind of operation (esophagectomy, gastrectomy, colectomy, rectal resection, pancreatic resection, or hepatectomy), and for patients with a history of a thromboembolic event.

#### Methods in analysis to handle protocol non-adherence and any statistical methods to handle missing data {20c}

The primary analysis data set is the intention-to-treat population. This data set contains all patients who have been enrolled in the clinical trial and randomized. The secondary analysis data set is derived from the per-protocol population. This data set includes all patients who have been treated according to the protocol during the whole duration of the study and reached a defined endpoint. The tertiary analysis data set (safety population) contains all patients who have received at least one dose of study medication. There are no specific statistical methods stipulated to handle missing data, because the proportion of patients with missing endpoint data is expected to be very low.

#### Plans to give access to the full protocol, participant-level data, and statistical code {31c}

Access to the full study protocol and statistical code will be granted upon reasonable request to the principal investigator. In accordance with data protection regulations, de-identified individual participant data will be shared with other researchers upon reasonable and justified request. It is planned to store de-identified individual participant data on the B2SHARE repository of the EUDAT collaborative data infrastructure.

### Oversight and monitoring

#### Composition of the coordinating center and trial steering committee {5d}

All trial activities are managed by a trial steering committee consisting of the principal investigator, two more authors of the study protocol, and two representatives from participating study sites. The trial steering committee decides, among other issues, about the recruitment and initiation of additional study centers and the modification to the study protocol following DSMB advice or due to other requirements. The committee convenes every 3 months during the entire trial period.

KKS Halle supports the trialists in all matters concerning the clinical trial including administrative project management, data management, monitoring, safety management, statistical analysis, and the performance of administrative tasks and duties.

#### Composition of the data monitoring committee, its role and reporting structure {21a}

An independent Data Safety Monitoring Board (DSMB) has been established to monitor safety data during the course of the clinical study. It comprises one expert each from surgery, anesthesiology, transfusion medicine, and biostatistics as well as a patient representative. The DSMB will receive regular information on safety events occurring in trial participants, in particular details on all reported SAEs, every 3 months during the trial period, and then convene for virtual meetings. This anonymized information will be prepared by the KKS. Moreover, if deemed necessary after due consideration by all of its members, the DSMB may initiate an unplanned interim analysis regarding safety and efficacy at any time point during the trial. The DSMB will give recommendations to the coordinating investigator for continuation, discontinuation, modification, or termination of the study.

All members of the DSMB are completely independent of the trial steering committee and investigators participating in the conduct of the trial. Their work is not subject to any directives by the aforementioned persons. In addition to its safety tasks, the DSMB provides the funding agency every 6 months with information about the trial progress and, if deemed necessary, provides advice regarding modifications of the original funding and time plan.

The composition and responsibilities of the DSMB and the structure and procedures of its meetings are laid down in a DSMB charter, which is available upon request from the principal investigator.

#### Adverse event reporting and harms {22}

Any adverse event (AE) occurring from IMP administration to the end of follow-up has to be documented. All AEs have to be followed until resolution/stabilization, improvement is not to be expected or end of study for the respective patient. AEs have to be recorded in the patient records and eCRF. The investigator is responsible for the assessment of the AE regarding severity, seriousness, and causal relationship to the IMP. Therefore, the following has to be documented:Event (diagnosis/symptom/results, etc.) with start date (onset) and end date (or ongoing on final examination at the end of the study), date of awarenessSeverity according to the current version V5.0 of CTCAE:

Grade 1—mild: asymptomatic or mild symptoms, clinical or diagnostic observations only; intervention not indicated.

Grade 2—moderate: minimal, local, or non-invasive intervention indicated; limiting age-appropriate instrumental activities of daily living (ADL).

Grade 3—severe: medically significant but not immediately life-threatening; hospitalization or prolongation of hospitalization indicated; disabling; limiting self-care ADL.

Grade 4—life-threatening: urgent intervention indicated.

Grade 5—death: death related to AE.Causality—relationship to the IMP (only TXA arm) according to the investigator (related/not related): Reasonably possible/related: The event occurs with a reasonable time relationship to study medication intake. There is no reasonable explanation that the event is caused by disease or other drugs. Reasonably NOT possible/not related: The event occurs with a time relationship to study medication intake that makes a relationship improbable. Diseases or other drugs provide plausible explanationSerious/non-serious. If the event meets any of the seriousness criteria additional documentation and reporting is required (see below)Actions taken for AE itself and regarding the IMP (including temporary or permanent)Outcome of the event

For the classification of the adverse events, the MedDRA code system will be used by KKS Halle.

A serious adverse event (SAE) has to be documented if it occurred between IMP administration and the end of follow-up. Serious adverse reactions (suspicion for causality related to the IMPs) have to be documented and reported over the entire course of the study including the follow-up period (until Visit 3). Additionally, an SAE has to be reported immediately (i.e., within 24 h upon becoming aware of the event) to KKS Halle using a SAE reporting form. Additional information including the course and outcome of the event can be completed in the follow-up report (an identical form can be used). The investigator will provide additional information if requested by the ethics committee, the competent federal authority, or the sponsor. Details are provided in an SAE reporting manual.

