#### Concealment mechanism {16b}

Randomization via an online tool (secuTrial®) generating a randomization number will ensure that group assignment is unbiased and concealed from participants, treating physicians, investigators, and other study staff. The online tool will provide the randomization number, which is identical to the Study Medication Number/reference code of the investigative medicinal product (IMP) label. All vials with study medication look identical, so that it remains concealed if participants receive TXA or placebo.

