### Assignment of interventions: blinding

#### Who will be blinded {17a}

Trial participants, treating physicians, investigators, and other study staff will all be blinded regarding assignment to interventions.

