#### Procedure for unblinding if needed {17b}

Only in case of an urgent medical reason (e.g., intraoperative disseminated bleeding in which a therapeutic use of TXA is deemed indicated), unblinding is possible. Such unblinding can be done by opening the appropriate blinding envelope upon due justification by the site investigator. The sponsor must be informed by fax about unblinding and its justification immediately (within 24 h). After unblinding, the treating physicians are informed about the participant’s allocation to TXA or placebo and can act according to the best individual therapeutic practice.

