### Statistical methods

#### Statistical methods for primary and secondary outcomes {20a}

The primary endpoint will be compared in the intention-to-treat population between the two study arms with a logistic regression model including the treatment group, and the stratification variables type of operation (esophagectomy, gastrectomy, colectomy, rectal resection, pancreatic resection, hepatectomy) and type of planned surgical access (open, minimally-invasive) as covariates.

The secondary endpoints of postoperative in-hospital complications and mortality will be analyzed similarly. The number of transfused units of PRBCs, estimated intraoperative blood loss, length of hospital stay, operation time, anesthesia time, D-dimer levels, and quality of life will be analyzed using a linear regression model including treatment group, type of operation, and type of surgical access as covariates. In case of heavy skewness in the outcome data, the outcome variables will be transformed to reduce skewness. All results for secondary outcomes will be interpreted in an exploratory sense. Dichotomous outcomes will be reported as absolute and relative frequencies and continuous variables by means, medians, standard deviations, and ranges. Time to transfusion will be compared between both arms using time-to-event analysis.

A safety analysis will be carried out by comparing the frequency of all adverse events and adverse events attributed to the intervention between the two study arms. Patients with a history of thromboembolic events will be analyzed as a subgroup of special interest.

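### Limiting the investigator's causality rating to the TXA arm cannot be done under the blind and leaves the planned between-arm comparison of attributed adverse events uninterpretable

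*Protocol article*

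**What the plan says.** All references are to the Protocol article.

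- **Adverse event reporting and harms {22}** first gives a general duty without any arm limit: "The investigator is responsible for the assessment of the AE regarding severity, seriousness, and causal relationship to the IMP". The list of items to document then narrows the causality item: "relationship to the IMP (only TXA arm) according to the investigator (related/not related".
- **Who will be blinded {17a}**: "Trial participants, treating physicians, investigators, and other study staff will all be blinded regarding assignment to interventions".
- **Concealment mechanism {16b}**: "All vials with study medication look identical, so that it remains concealed if participants receive TXA or placebo".
- **Section {17b}**, on breaking the code, is restrictive: "Only in case of an urgent medical reason (e.g., intraoperative disseminated bleeding in which a therapeutic use of TXA is deemed indicated), unblinding is possible".
- **Statistical methods for primary and secondary outcomes {20a}** defines the safety analysis as "comparing the frequency of all adverse events and adverse events attributed to the intervention between the two study arms".
- **Methods in analysis to handle protocol non-adherence {20c}** defines the safety population as one that "contains all patients who have received at least one dose of study medication", which takes in both arms.

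**The concern.** Three instructions do not fit together. The causality item is for one arm only. The person who completes it does not know the arm. The analysis needs the item in both arms.

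Blinded attribution is informative because the placebo arm shows how often investigators call an event drug-related when no active drug was given. Without that reference, the number of attributed events on TXA has nothing to be compared with. Safety of TXA is a stated secondary objective (Objectives {7}), and the comparison of attributed events is one of the two that section {20a} plans for it. This is also an instruction on what sites record, so a later analysis plan cannot restore blinded placebo ratings that were never made.

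**Working it through.** **1. Can the instruction be followed?** It requires the investigator to know who is on TXA. Section {17a} blinds the investigator, section {16b} makes the vials indistinguishable, and section {17b} opens the code only for an urgent medical reason; rating an adverse event is not named as one. No section gives the rating to an unblinded assessor. So the instruction cannot be followed within the protocol's own rules.

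**2. Can the planned comparison use the result?** There are three possibilities:

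| What happens in practice | Placebo arm in the {20a} comparison |
|---|---|
| Placebo events are not rated | Not assessed; no comparison possible |
| Unrated placebo events are counted as unrelated | Zero |
| All events are rated blind, placebo ratings discarded after unblinding | Zero if the discarded ratings are treated as unrelated |

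Only a fourth course, rating everyone blind and keeping all ratings, gives a valid comparison. The parenthesis rules that course out.

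**3. Arm size for an illustration.** The document gives no figure for attributed events, so only the arm size comes from it. Sample size {14} assumes 30% against 20%, two-sided 5% and 90% power:

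- n = [1.960·√(2·0.25·0.75) + 1.282·√(0.3·0.7 + 0.2·0.8)]² / 0.10² = 392 per group without continuity correction.
- With correction, n′ = (n/4)·[1 + √(1 + 4/(n·0.10))]² = 412, the stated figure.
- 412/(1 − 0.03) = 424.7, so 425, also as stated.

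**4. The zero case.** With k attributed events among 425 on TXA and 0/425 on placebo, the two-sided Fisher p is 2·C(425,k)/C(850,k):

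- k = 5: p = 0.062
- k = 6: p = 0.031

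Six events are enough for p < 0.05. An uncorrected χ² test gets there at k = 4 (p = 0.045).

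**5. How often would this arise without a true difference?** Suppose blinded investigators would attribute an event in the same proportion r of patients in both arms, and the placebo ratings are lost and counted as zero. The chance of a spurious significant excess is P(X ≥ 6) with X ~ Binomial(425, r). The rates r are assumptions:

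| Assumed r | Expected on TXA (425·r) | Chance of Fisher p < 0.05 |
|---|---|---|
| 0.5% | 2.1 | 2% |
| 1% | 4.25 | 25% |
| 2% | 8.5 | 85% |
| 3% | 12.75 | 99% |
| 5% | 21.25 | >99.9% |

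**The case against.** The best defence is that the parenthesis is loose drafting. Section {22} gives the investigator the causality judgement for the adverse event without an arm limit. Its definitions of related and not related are tied to intake of study medication, a term that section {16b} uses for vials of either content. The author may have meant only that a true reaction to TXA cannot occur on placebo. If sites cannot tell the arms apart, they may well rate everyone. This has force on intent. It does not repair the text: the milder reading is nowhere stated, and setting placebo ratings aside after unblinding would still spoil the comparison in {20a}.

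The illustration also has limits, and these stand. Section {20a} names no test for adverse events, so the p-values are a yardstick and not the plan's own. The definition of related is strict: a reasonable alternative explanation in disease or other drugs excludes it. After major surgery that could keep the attributed rate low, near the top of the table, where a false signal is uncommon.

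Two stronger readings are tempting and not supported:

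- A reader might infer that the code must be broken to rate events, exposing staff who decide on transfusion and so biasing the primary endpoint. Section {17b} closes that route, and no section says that the causality raters are the people who decide on transfusion.
- A reader might infer that the placebo count is fixed at zero, so that TXA appears harmful by construction. Strictly, the placebo value is not assessed. It becomes zero only if unrated events or discarded ratings are treated as unrelated, and the document prescribes neither.

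Serious adverse reactions do rest on the same judgement: "Serious adverse reactions (suspicion for causality related to the IMPs) have to be documented and reported over the entire course of the study". But section {22} requires every SAE to be reported within 24 hours whatever its attribution, and the DSMB receives details of all reported SAEs every 3 months (section {21a}). SAE reporting is therefore not compromised.

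**Conclusion.** The point holds as an internal contradiction. The restriction in {22} cannot be applied by the blinded investigators of {17a} and conflicts with the comparison in {20a}. As written, that comparison of attributed adverse events is not interpretable. This conclusion rests on the text alone and needs no assumed rate.

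The numerical size applies only to the zero case. It assumes 425 treated patients per arm, equal true attribution in both arms and a Fisher test. The chance of a false signal then runs from about 2% at an attributed rate of 0.5% to over 99% at 5%; the document does not say where in this range the trial would fall.

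The damage is confined to one safety comparison. The primary endpoint, the sample size, the comparison of all adverse events and SAE reporting stand. The correction should be made, but the defect does not threaten the main result.

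**What to change.** - In {22}, delete the parenthesis that restricts the rating to the TXA arm.
- State that the investigator rates causality to the blinded study medication, TXA or placebo, for every AE and SAE in both arms.
- In {20a}, state that the comparison of attributed events uses ratings made before unblinding, and flag any rating made after an emergency unblinding under {17b}.

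The cost is a wording change in the protocol and in the eCRF and SAE forms, a notice to sites, and a little more rating work. Recruitment began in June 2024 (Trial status), so sites should also be asked whether any events were left unrated; missing ratings can be completed blind only while the code is unbroken. If sites already rate everyone, the change simply brings the text into line with practice.

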Tranexamic acid (TXA), a lysine analogue inhibiting plasminogen activation and providing clot stability, has been used to reduce hemorrhage. There is ample evidence from randomized controlled trials (RCTs) and meta-analyses that TXA use is associated with reduced blood loss in orthopedic [8–11], cardiac [12], urological [13], and gynecological surgery [14]. For example, an RCT showed that the probability of being transfused PRBCs after surgery for hip fracture experienced a relative reduction of 22% [15]. While a meta-analysis comprising 104 RCTs on all surgical interventions found a 34% relative reduction in blood loss with only small differences between different operations [16], another meta-analysis of 129 RCTs demonstrated a 38% lower transfusion probability in patients who received TXA [17]. A systematic review and meta-analysis comprising 216 RCTs comparing TXA to placebo or no treatment showed a significant decrease in overall bleeding mortality with no increase in the risk of thromboembolic events as the main adverse event of concern [18]. The hitherto largest RCT including 9.535 patients undergoing non-cardiac surgery showed a 2.6% lower risk for a composite outcome of bleeding in patients receiving TXA. Subgroup results for abdominal surgery were however not presented [19].

There are few trials evaluating the specific effect of TXA administration in abdominal surgery. Four trials were conducted in patients undergoing liver transplantation and one in patients undergoing elective liver resection. While three trials showed a significantly lower blood loss and transfusion requirement for TXA [20–22], two underpowered trials failed to show a difference [23, 24]. In a retrospective series of patients undergoing resection of colorectal liver metastases, a 41% reduction in transfusion probability was found following TXA administration [25], whereas another retrospective series showed no differences in hemoglobin drop and transfusion probability [26]. One RCT on TXA use in pancreatoduodenectomy failed to show a reduction in estimated blood loss [27]. Ongoing RCTs on the use of TXA in abdominal surgery without available results comprise TXA application in cytoreductive surgery (NCT03646474), colorectal cancer surgery (NCT03606785), liver resections (NCT02261415), and bariatric sleeve gastrectomy (NL8029).

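### The two causality ratings give no 'related' rating to a well-timed adverse event that also has a plausible disease or drug cause, and they conflict with the protocol's own standard for serious adverse reactions

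*Protocol article*

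**What the plan says.** In the protocol article, *Adverse event reporting and harms {22}*, the investigator documents the "relationship to the IMP (only TXA arm) according to the investigator (related/not related"). Two ratings exist.

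- The rating labelled reasonably possible/related has two sentences: "The event occurs with a reasonable time relationship to study medication intake", and "There is no reasonable explanation that the event is caused by disease or other drugs".
- The rating labelled reasonably not possible/not related also has two: "The event occurs with a time relationship to study medication intake that makes a relationship improbable", and a further sentence saying that diseases or other drugs plausibly explain the event. No 'and' or 'or' joins them.

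Later in {22}, a different standard appears: "Serious adverse reactions (suspicion for causality related to the IMPs) have to be documented and reported over the entire course of the study".

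The ratings feed the analysis. *Statistical methods {20a}* plans a safety analysis by "comparing the frequency of all adverse events and adverse events attributed to the intervention between the two study arms". *Background and rationale {6a}*, citing a meta-analysis, reports "no increase in the risk of thromboembolic events as the main adverse event of concern".

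**The concern.** A two-level rating works only if every event falls into exactly one level and the levels mean what their labels say. Here the label for 'related' speaks of reasonable possibility, but its definition asks that competing explanations by disease or drugs be excluded. Those are different thresholds. After major resection, an event can be well timed, possibly due to the study drug and possibly due to the patient's disease, all at once. The rule has no place for that event among the related ones.

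Two uses of the rating are at stake. The attributed comparison in {20a} serves the safety objective stated in {7}; a rule that removes events with competing causes makes the count of related events low for reasons unconnected with the drug's true effect. And an investigator who follows the definition literally may not pass on as a serious adverse reaction an event for which a suspicion exists.

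**Working it through.** The plan gives no figure on this point, so there is none to reproduce. The check is a truth table.

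Inputs, all from {22}: T = timing is reasonable; A = disease or another drug offers a reasonable or plausible explanation. Rules:

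- Related = T and not A (the two sentences read jointly).
- Not related = (not T) and A under the 'and' reading; (not T) or A under the 'or' reading.

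| Timing reasonable | Disease/drug explanation | Related? | Rating if 'and' | Rating if 'or' |
|---|---|---|---|---|
| yes | no | yes | related | related |
| yes | yes | no | fits neither | not related |
| no | yes | no | not related | not related |
| no | no | no | fits neither | not related |

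Under 'and', 2 of the 4 combinations have no rating. Under 'or', all four have one, but the second row is rated not related although the label for that rating says a relationship is not reasonably possible. In neither case is the second row related.

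Applied to thromboembolism: adverse events are documented from drug administration to the end of follow-up, which {18a} places at discharge or postoperative day 30, whichever comes first. Timing will therefore often be accepted as reasonable. Eligibility ({10}) covers oesophageal, gastric, colorectal, pancreatic and hepatic resections, and {6a} discusses oncological patients, so the underlying disease will often be offered as an explanation. Many such events then fall in the second row.

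Set against the serious-adverse-reaction sentence: that sentence needs only suspicion. A second-row event can be suspected, and so qualify there, while the rating definition bars it from 'related'. The section does not say which governs.

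Routes that do not depend on the rating:

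- {11d} requires an AE or SAE report for a thromboembolic event.
- {22} says "an SAE has to be reported immediately (i.e., within 24 h upon becoming aware of the event) to KKS Halle", with no causality condition.
- {21a} sends the DSMB details of all reported SAEs every 3 months.
- {20a} also compares all adverse events, and analyses the secondary endpoints of complications and mortality by regression, regardless of attribution.

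**The case against.** The best defence is that the labels are the operative text. Reasonably possible and reasonably not possible are complementary, they fit the suspicion standard, and the sentences beneath may be mere descriptors. The passage is a flattened list, so layout that clarified the logic may have been lost. This has some force: an investigator who rated by the label alone would do roughly the right thing. But the sentences are the only definition given, and they contradict the label for the commonest difficult case. If the two 'related' sentences were read as alternatives and the two 'not related' sentences jointly, the categories would be complementary and the second row would be related. That needs different connectors in two parallel definitions, and it would also make an ill-timed event related whenever no other explanation exists. It is not the plain reading, and its possibility is a reason to state the connectors.

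A reader might infer more than the text supports, in two ways. First, that no thromboembolic event in this trial could ever be rated related, because surgery always explains it. The exclusion names disease or other drugs, and surgery is neither; patients are eligible by operation, not by diagnosis. Loss is likely for many events but not automatic. Second, that such events vanish from safety oversight. The four routes listed above show that they do not. Under-identification of serious adverse reactions is a risk, not a stated result, and the SAE reporting manual that gives the details is not shown.

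It is also fair to object that the attributed comparison already fails because causality is rated only in the TXA arm. That is a separate defect, and lifting the restriction would leave these definitions as they are.

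**Conclusion.** The point holds as a defect in a stated rule. The causality ratings are not exhaustive under one reading and contradict their own label under the other. On both, a well-timed event with a plausible disease or drug cause is never related. The section also applies a lower standard to serious adverse reactions without reconciling the two. The effect on the attributed comparison is toward few related events, including for the adverse event of most concern.

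The conclusion assumes that the two sentences under 'related' apply jointly and that investigators follow the definitions rather than the labels. The share of events affected cannot be computed, because the documents give no rates of thromboembolism or of competing causes. A power comparison between a thromboembolism-specific test and a test of all adverse events would not measure this defect either: its result is the same whichever wording is used. The primary endpoint, the capture of adverse events and the reporting of SAEs are not affected. That the article shows no thromboembolism table is not part of the finding, since the analysis plan may contain one.

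**What to change.** In {22}, and in the SAE reporting manual if it repeats the wording, define the ratings so that every event has one and they match their labels and the suspicion standard:

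- Related: a causal contribution of the study drug is a reasonable possibility, even if disease or other drugs are also possible causes.
- Not related: there is no reasonable possibility of such a contribution.

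Recruitment began on 17 June 2024 (*Trial status*), so ratings already made under the current wording should be reviewed. Resolve the restriction of causality rating to the TXA arm at the same time; the attributed comparison cannot work without that. As a safeguard, report thromboembolic events by arm in the whole safety population regardless of attribution, if the statistical analysis plan does not already do so.

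The cost is one reworded definition, brief site retraining, the review of existing ratings and at most one extra table. The downside is that somewhat more events will be rated related.
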